#### Anticipated loss to follow up

In the Liverpool study, 148 patients were randomised to treatments; each was scheduled to receive four assessments by postal questionnaire (baseline, 3 months, 6 months, one year), making a total of 592 assessments in all. At the end of the trial, 541 of these assessments had been completed (including those completed on drop-outs), giving a loss to follow up of only 9%. Our patients will be required to complete a larger battery of assessments than those in the Liverpool study, which might reduce participation rates. On the other hand, we anticipate that the fact that interventions and assessment will take place in the patients' homes in this trial will reduce both failure to adhere to treatment and failure to complete assessments. To ensure that we have sufficient numbers to test our hypotheses, we have estimated a rate of 23% combined non-compliance and loss to follow-up (this being half-way between the 35% drop out rate reported in a previous primary care trial [22], and the 9% loss to follow up in our previous trial). To reduce loss to follow-up, we plan to ask patients to nominate a relative or friend who could be contacted to help us to trace them should they move away.

Some CFS/ME patient support groups have suggested that activity may be harmful to some CFS/ME patients [4], but no adverse outcomes have been reported from previous well-conducted treatment trials that have included adequately graded activity as a component of treatment [4]. The activity programme forming part of pragmatic rehabilitation is determined collaboratively by the patient and therapist, and always starts at a level less taxing than the patient can currently manage. Similarly, the rate at which activity is increased and the type of activity undertaken are determined by the patient in collaboration with the therapist. If there are any adverse reactions, these will be notified to the independent committees overseeing the trial (the Data Monitoring and Ethics and Trial Steering Committees) and to MREC, in accordance with agreed procedures.

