### Power analysis

We plan to recruit 120 patients for each treatment arm. Our power calculation was based on a comparison between pragmatic rehabilitation and treatment as usual. In the Liverpool hospital-based study [26], at 12 months after the start of treatment, on an intention to treat basis with previous scores assigned for dropouts, 57% of intervention group patients and 6% of control group patients were classified as "no longer cases" (i.e. scored 4 or less on the Fatigue Scale and 75% or more on the SF36 physical functioning scale). On the basis of previous studies, we would expect to see a bigger improvement in patients receiving treatment as usual in primary care [7,9]. We have also taken a more conservative estimate of the proportion of patients likely to improve in the pragmatic rehabilitation condition; we believe that a 20% difference in improvement rates between intervention and control patients would be of interest to the NHS. A two-group χ^2 ^test with a 0.05 two-sided significance level will have 80% power to detect the difference between an intervention group proportion of 50% improved and a treatment as usual group proportion of 30% improved, when the final sample size is 93 per group. Allowing for a rate of loss to follow-up of 23% in the treatment as usual group, the sample size required is 120 per group.

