#### Analysis of quantitative data

Baseline comparability of the three treatment groups will be described, but no significance testing will be conducted. Acceptance of and adherence to treatment will be described. Patients in the pragmatic rehabilitation and supportive listening arms will be deemed to have accepted treatment allocation if, after randomization, they embark on treatment, that is they make themselves available for the first treatment session. Patients in the treatment as usual arm will be deemed to have accepted treatment if, after randomization, they agree to return to their GP's care. To measure adherence to treatment, in the pragmatic rehabilitation and supportive listening arms, the number of home visit sessions and number of telephone calls that in the opinion of the therapist constituted an intervention session will be counted. No attempt will be made to assess adherence further than this. In the absence of any protocol violation (e.g. receiving a systematic psychological therapy for CFS/ME), patients in the treatment as usual arm will be deemed to have adhered to treatment. Missing outcome data will be described in relation to patient baseline characteristics and adherence to treatment.

Descriptive statistics for outcome measures will be presented. The main analyses will be carried out using all patients randomized using the principle of Intention-To-Treat (ITT). With three groups (Pragmatic Rehabilitation – PR, Supportive Listening – SL and Treatment as Usual – TAU) we will have two degrees of freedom to test for group differences. Following a global test to determine whether the three groups are different, pragmatic rehabilitation will be contrasted with supportive listening. If there is no evidence of any difference in outcome between pragmatic rehabilitation and supportive listening, they will be jointly contrasted with treatment as usual. If pragmatic rehabilitation and supportive listening differ in their outcomes, then they will be separately compared with treatment as usual. Effect sizes and confidence intervals will be reported for each group

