Sensitivity of the treatment effect estimates to potential biases arising from missing outcome data will be evaluated by the use of inverse probability weighting [49,50]. This assumes that the missing data mechanism is ignorable – i.e. Missing at Random (MAR). We will also carry out a likelihood-based analysis of all available data using *Mplus *[51] again assuming that the missing data mechanism is ignorable.

A supplementary set of analyses will be undertaken to assess the effect of non-adherence to allocated treatment (again taking account of sensitivity to assumed missing data mechanisms) in order to estimate treatment effects in those patients who have complied with randomization (the estimation of the Complier Average Causal Effect – CACE – as opposed to the Average Causal Effect – ACE – as estimated using ITT methods). We have provided detailed examples of this approach elsewhere [52,53].

All analyses to estimate treatment effects will be variations on an analysis of covariance with the exact form depending on whether outcome is binary or quantitative. Covariates will include whether the patient is ambulatory or not, and whether the patient fulfils London ME criteria or not.

Supplementary, exploratory analyses will be carried out to determine predictors of response to treatment. These will include, but may not be restricted to, (1) dichotomous variables such as membership of self-help group, whether ambulatory or not, whether the patient fulfilled London ME criteria, presence or absence of psychiatric diagnosis (e.g. depression); and (2) continuous variables such as illness duration, score on HAD depression scale, score on social support scale, and baseline illness beliefs scores. Analysis will take place once, after data collection is complete. There are no proposed interim analyses.

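### Both stated missing-outcome analyses assume an ignorable mechanism, so their agreement says nothing about non-ignorable loss, and no non-ignorable mechanism is named for the ITT or CACE estimates

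*Protocol article*

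**What the plan says.** Under Analysis of quantitative data, the protocol article states the aim in general terms: "Sensitivity of the treatment effect estimates to potential biases arising from missing outcome data will be evaluated by the use of inverse probability weighting". It then qualifies the weighting analysis: "This assumes that the missing data mechanism is ignorable", that is, missing at random (MAR). A second analysis, likelihood-based and using all available data in Mplus, is added, "again assuming that the missing data mechanism is ignorable".

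The next paragraph turns to the complier average causal effect (CACE) and says that this work will be done "again taking account of sensitivity to assumed missing data mechanisms". It names no mechanism.

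Earlier in the same section comes a descriptive step: "Missing outcome data will be described in relation to patient baseline characteristics and adherence to treatment".

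The expected amount of missing data is described in two ways. Power analysis has: "Allowing for a rate of loss to follow-up of 23% in the treatment as usual group, the sample size required is 120 per group". Anticipated loss to follow up has: "we have estimated a rate of 23% combined non-compliance and loss to follow-up". That second section also reports 9% loss in the earlier hospital trial.

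**The concern.** The aim covers bias from missing outcomes in general, but each tool offered rests on one assumption: given what has been observed, response at 70 weeks does not depend on the unseen score. Comparing two methods that share an assumption does not test it. If patients on pragmatic rehabilitation (PR) who are doing badly at 70 weeks stop responding, for reasons that baseline data, 20-week scores and adherence do not capture, both estimates move in the same direction by about the same amount.

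The risk is in the reporting. Close agreement between the weighted and likelihood results could be presented as robustness to missing data, when it would show only that two MAR methods agree. The primary outcomes are self-reported scores a year after treatment ends, so some loss related to outcome is possible. The article gives no evidence that it will happen.

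**Working it through.** **Inputs.** From Power analysis: 50% improved on PR, 30% on treatment as usual (TAU), two-sided 0.05, 80% power, 93 evaluable and 120 recruited per arm, 23% loss. From Anticipated loss to follow up: 541 of 592 assessments completed in the earlier trial, so 51/592 = 8.6%, given as 9%. The shifts for missing patients are assumptions, because the article gives none.

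**The plan's own figure.** Pooled-variance formula without continuity correction:
n = [1.960 × √(2 × 0.4 × 0.6) + 0.842 × √(0.5 × 0.5 + 0.3 × 0.7)]² / 0.20² = (1.358 + 0.571)² / 0.04 = 93.
Inflation: 93/0.77 = 120.8, against a stated 120 (120 × 0.77 = 92.4). Both figures reproduce, give or take one patient.

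**Do the two methods differ when MAR fails?** A simulation of 400,000 patients in two arms had a true effect of 0.50 SD, one measured baseline variable, and about 22–23% missing. Regression standardisation stood in for the likelihood analysis.

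| Missingness | Unadjusted complete cases | Adjusted complete cases | Weighted | Likelihood-type |
|---|---|---|---|---|
| Depends on baseline in the PR arm (MAR) | 0.58 | 0.50 | 0.50 | 0.50 |
| Depends on the outcome in the PR arm (not MAR) | 0.71 | 0.66 | 0.66 | 0.66 |

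In the first row, weighting exposes and removes a real bias. In the second, the two planned methods agree and are both wrong by 0.16 SD.

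**Size on the design rates.** Hold TAU at 30%, let m be the missing fraction and q the improvement rate among missing PR patients. Then
D = (1 − m) × 0.50 + m × q − 0.30.

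- m = 0.23, q = 0.30: 0.385 + 0.069 − 0.30 = 0.154
- m = 0.23, q = 0.10: 0.385 + 0.023 − 0.30 = 0.108
- m = 0.09, q = 0.30: 0.455 + 0.027 − 0.30 = 0.182
- m = 0.09, q = 0.10: 0.455 + 0.009 − 0.30 = 0.164

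Approximate p-values use the pooled z-test at the observed number per arm, 120 × (1 − m), which is 92.4 or 109.2. This is not a full imputation variance.

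| Shift in missing PR patients (points) | 23% missing: D, p | 9% missing: D, p |
|---|---|---|
| 0 (MAR) | 20.0, 0.006 | 20.0, 0.003 |
| −20 (q = 30%) | 15.4, 0.031 | 18.2, 0.006 |
| −30 (q = 20%) | 13.1, 0.065 | 17.3, 0.009 |
| −40 (q = 10%) | 10.8, 0.125 | 16.4, 0.013 |
| −50 (q = 0%) | 8.5, 0.22 | 15.5, 0.018 |

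At 23% missing, p reaches 0.05 at a shift of about −26 points, which means missing PR patients improving at about 24%. At 9% missing, even the largest possible PR-only shift leaves p = 0.018.

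If both arms may take any value, the bounds on D are −7.6 to +38.4 points at 23% and +9.2 to +27.2 points at 9%.

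The 9% averages over four assessments, one of them baseline. If every baseline had been completed, loss over the three later ones would be 51/(3 × 148) = 11.5%, so 9% is a favourable guide to a single late assessment.

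**The case against.** Most of the case on the other side stands, and it limits how far the point goes.

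- The article declares the MAR assumption each time, so nothing is hidden. It also says that pre-determined plans are lodged with the oversight committees; these are not shown and may contain more. Even so, the article itself fixes the aim, the methods and their assumption, and the aim as worded is wider than the methods.
- A reader might infer that the two analyses can show no sensitivity at all. That is too strong. Against an unweighted analysis, weighting can reveal bias from measured predictors, as the first row of the simulation shows.
- Some of the feared loss may be MAR. Patients who saw no benefit may already have a 20-week score, and the likelihood analysis uses all available data. Adherence is also recorded. A loss rate that differs by arm is not in itself a departure from MAR, because arm is known.
- Stopping therapy is not the same as a missing outcome. The earlier trial's completed assessments included some from drop-outs, and the article expects home assessment to reduce non-completion.
- The 23% is combined non-compliance and loss in one section and loss to follow-up in another, so treating it all as missing outcomes may overstate the problem.
- The scenarios penalise PR alone; worse outcomes among missing TAU patients would offset them. They also use a binary improvement rate, whereas the clinical primary outcomes are scores.
- The CACE sentence speaks of mechanisms in the plural and the section cites worked examples elsewhere. Whether these include a non-ignorable mechanism cannot be judged from the article, so calling that promise empty would go too far. What can be said is that none is named.

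**Conclusion.** The point holds in a limited form. The stated strategy can address missingness that depends on measured variables. It cannot address non-ignorable loss, and agreement between the two methods should not be reported as if it did.

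The size depends on how much is missing. At 23%, a PR-only shift of about 26 points removes significance at the design effect, and shifts of 20 or 40 points leave 15.4 or 10.8 points of the 20. At 9%, the same shifts leave 18.2 or 16.4 points and the conclusion is robust to any shift in PR alone. These figures assume 50% and 30% observed improvement, TAU held at 30%, equal missing fractions in the two arms, and shifts chosen for illustration.

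A reader might go further and infer that selective loss could manufacture a benefit. The PR-only scenarios do not show that: each starts from a 20-point difference and leaves a positive one. Only the extreme bound at 23%, with every missing PR patient unimproved and every missing TAU patient improved, changes the sign. This is a worthwhile, inexpensive improvement to the plan and does not invalidate the main analysis.

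**What to change.** Keep both MAR analyses. Before the single planned analysis, pre-specify one departure analysis of the 70-week SF-36 physical functioning and fatigue scores: either delta-adjusted multiple imputation or a tipping-point analysis. Vary the shift over a stated grid separately in each arm, including supportive listening and TAU, and report the shift at which the conclusion changes. State in the CACE paragraph which missing-data mechanisms are meant.

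If no such analysis is wanted, reword the aim so that it claims sensitivity only to missing-at-random mechanisms. If the lodged plan already contains a non-ignorable analysis, a reference to it is enough.

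In either case, reconcile the two descriptions of the 23%, so that the expected fraction of missing outcomes is clear.

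The cost is a little programming and one extra table. No new data and no change to the sample size are needed.

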### The participants – inclusion and exclusion criteria

Patients aged 18 and over who fulfil the Oxford criteria for CFS [1] are eligible for inclusion in the trial, with no upper age limit. These criteria require that patients have a principal complaint of severe, unexplained fatigue, of new onset, persisting or relapsing over a period of at least six months, which results in a substantial impairment to previous levels of activity and affects both mental and physical functioning. We have chosen the Oxford criteria for inclusion as they are simpler for GPs to operate than the CDC criteria [2], but at baseline assessment we also ascertain whether patients meet the slightly more restrictive CDC diagnostic criteria. The CDC criteria, in addition to the above, require that patients have at least four from a list of eight other symptoms, concurrent with the fatigue [2]. We also record whether patients fulfil London ME criteria at baseline [33]. We decided not to use the recently published Canadian criteria [34], as these have not yet been validated for research purposes. Both the CDC and the Oxford criteria require that possible medical and psychiatric causes for fatigue are excluded by the taking of a thorough history, physical examination and a battery of tests. Participating GPs are provided with a brief protocol to enable them to carry out these assessments. As GPs may experience difficulty in determining patients' levels of activity, we require that patients are sufficiently functionally impaired to score 70% or less on the SF-36 physical functioning scale [35]. Additionally, patients are required to score 4 or more on the 11-item Chalder fatigue scale [36]. In accordance with the Oxford and CDC criteria [1,2], patients whose fatigue is explained by any active medical condition are excluded, as are patients with schizophrenia, bipolar disorder, dementia, eating disorders or substance abuse. Patients with active suicidal ideation (i.e. within the last month) or with antisocial, borderline or paranoid personality disorders are excluded because our nurse therapists are not trained to treat these conditions. The following patients are also excluded: patients who cannot read or write English sufficiently well to participate in treatment or complete the assessment measures; patients who are incapable of giving informed consent; patients who are currently undertaking systematic psychological therapies for CFS/ME or who have received pragmatic rehabilitation therapy within the past year. Patients with mild to moderate depression and/or anxiety disorders are not excluded. Patients with comorbid conditions (for example, orthopaedic problems) that might be exacerbated by the activity programme are not excluded, but the advice given to them is tailored accordingly.

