### The baseline assessment

The baseline assessment serves two purposes – firstly to ensure that patients recruited to the trial meet study criteria, and secondly to obtain baseline measures on all our outcomes. The schedule for the baseline assessment and subsequent assessments is shown in Table 1. If there is any doubt as to whether the patient fulfils criteria for entry to the study, the research assistant consults with medically qualified members of the team and/or the referring GP, and if necessary the patient can be referred back to the GP for further information or tests. Once we are satisfied that the patient fulfils study criteria, the trial manager notifies the randomisation service.

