### Randomisation

Randomisation of individual patients as they are recruited to the trial is carried out by an independent randomisation unit based at Christie Hospital in Manchester, in consultation with the trial statistician, and in accordance with a randomisation protocol. The procedure uses randomised permuted blocks (with randomly-varying block sizes of 9, 12, 15 or 18), after stratification based on whether the patient is ambulatory or not (not ambulatory being defined as using a mobility aid on most days), and on whether the patient fulfils London ME criteria or not. There are therefore four strata in total. Where applicable, patients are assigned to therapists in a simple random fashion according to the therapists' availability. The trial manager is informed of randomisation, and group membership is conveyed to the designated nurse-therapist, if appropriate. The GP is informed of randomization and sent a copy of the patient consent form.

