### Outcome measures

Patients are assessed at entry to the trial (week 0), within one week of the end of treatment (20 weeks), and then one year after finishing treatment (70 weeks). Assessments are carried out by trained researchers who are blind to the arm to which the patient has been randomised. Assessment at week 70 is required because short-term assessments of outcome in a chronic health condition such as CFS/ME can be misleading. Additionally, psychological treatments such as CBT become more effective over time [13] and we wish to be able to determine whether that is the case for our interventions. The primary outcome point is 70 weeks.

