#### Primary outcome measures

The primary outcome measures are patient-rated to avoid observer bias. These are (1) score on the physical functioning scale of the SF-36 [35], (2) cost-effectiveness using the Euroqol [40] and (3) the score on the 11-item Fatigue Scale [36]. An improvement of 50% or more on the SF-36 physical functioning scale, or a score of 75% or more on that scale, will be considered a clinically significant improvement.

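### The article names the two stratification factors as covariates but not the baseline score of the outcome; adding it would be a free gain in precision

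*Protocol article*

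**What the plan says.** All statements are in the Protocol article.

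- **Model (Analysis of quantitative data).** "All analyses to estimate treatment effects will be variations on an analysis of covariance with the exact form depending on whether outcome is binary or", the alternative being a continuous score.
- **Covariates (same section).** "Covariates will include whether the patient is ambulatory or not, and whether the patient fulfils London ME criteria or not".
- **Randomisation.** Blocks are permuted "after stratification based on whether the patient is ambulatory or not (not ambulatory being defined as using a mobility aid on most days"; London ME criteria are the second factor, giving four strata. The two named covariates are therefore exactly the two stratification factors.
- **Baseline data (The baseline assessment).** The visit serves to confirm eligibility and "secondly to obtain baseline measures on all our outcomes".
- **Outcomes (Primary outcome measures; Outcome measures).** The primary clinical outcomes are quantitative: "1) score on the physical functioning scale of the SF-36" and "the score on the 11-item Fatigue Scale". On timing: "The primary outcome point is 70 weeks".

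No section names the baseline value of the outcome as a covariate, and none excludes it. The opening paragraph of the Analysis plan refers to pre-determined plans lodged with the two oversight committees. Those plans are not shown.

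**The concern.** The baseline value of a patient-rated score is usually among the strongest predictors of the same score at follow-up. Two yes/no factors, one for use of a mobility aid and one for a diagnostic label, can carry only part of that information. The Discussion expects patients from the whole range of illness severity, so baseline scores should vary within each stratum.

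If the models adjust for the two factors and nothing else, variation that the baseline score could explain stays in the residual. The standard errors for the two primary clinical scores are then larger than the collected data require, and a chance imbalance in baseline severity is not adjusted for. At stake is efficiency: wider confidence intervals than necessary for the contrasts among pragmatic rehabilitation, supportive listening and treatment as usual.

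**Working it through.** **1. The plan's own figure.** Inputs from Power analysis: 50% versus 30% improved, two-sided 0.05, 80% power, chi-squared test, 93 per group, 23% loss.

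n = [1.960·√(2·0.40·0.60) + 0.8416·√(0.50·0.50 + 0.30·0.70)]² / 0.20²
= [1.960·0.6928 + 0.8416·0.6782]² / 0.04
= 1.9287² / 0.04 ≈ 93.

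Power at 93 per group is 80.0%. Inflating for loss gives 93/0.77 = 120.8, against 120 stated. The figure reproduces and uses no covariate, so it is the same whether or not baseline is adjusted for.

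**2. Reference point for a quantitative score.** With 93 per arm and no baseline adjustment, the standardised difference detectable with 80% power is 2.802·√(2/93) = 0.411 SD. This is a yardstick only; the trial was not sized on it.

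**3. Effect of adding the baseline score.** Let r be the within-arm correlation between the baseline and 70-week scores. The article gives no value, so r is assumed over a range. Adjustment multiplies the residual variance by 1 − r² and the standard error by √(1 − r²). The strata are taken here to explain nothing.

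| r (assumed) | 1 − r² | SE smaller by | Detectable difference, 0.411·√(1 − r²) | Power at 0.411 SD | 93 per arm acts like 93/(1 − r²) |
|---|---|---|---|---|---|
| 0 | 1.00 | 0% | 0.411 SD | 80.0% | 93 |
| 0.3 | 0.91 | 4.6% | 0.392 SD | 83.6% | 102 |
| 0.5 | 0.75 | 13.4% | 0.356 SD | 89.9% | 124 |
| 0.7 | 0.51 | 28.6% | 0.293 SD | 97.5% | 182 |

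The percentage cut in the standard error does not depend on the sample size; the last three columns do.

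**4. Allowing for what the strata already explain.** Ambulatory status is itself a marker of physical function, so the gain over a model with the two strata is smaller. The variance ratio is (1 − R² of the full model)/(1 − R² of the strata). Taking a total R² of 0.30 as an assumed example:

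- strata explain 0%: 0.70/1.00 = 0.70, SE ratio 0.837, about 16% smaller;
- strata explain 10%: 0.70/0.90 = 0.778, SE ratio 0.882, about 12% smaller;
- strata explain 20%: 0.70/0.80 = 0.875, SE ratio 0.935, about 6% smaller.

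The table in step 3 is therefore an upper figure for each r.

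**5. Scope.** The 1 − r² relation applies to the linear model for the quantitative scores. It does not carry over to a logistic model for the binary improvement criterion, so no figure is given for that outcome.

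**The case against.** The strongest reply is that the covariate sentence is an open list. It says what the covariates include and excludes nothing. The label analysis of covariance is commonly used for adjusting a follow-up score for its baseline. A complete covariate list is ordinary content for the lodged plans that the article condenses. A reader might infer that baseline is deliberately left out and precision is being given away. The documents do not establish that, and this part of the reply stands.

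It does not dispose of the point. The article did not leave the covariates wholly to the lodged plan: it stated some and omitted the one that usually matters most. In the next paragraph, on exploratory predictors, the list is marked explicitly as not exhaustive; the covariate sentence carries no such marking. That contrast does not close the list, but it lets a reader take the two strata as the adjustment set.

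The size of the gain is also open to challenge, and rightly. No correlation is given. The entry rules narrow the baseline range (patients must "score 70% or less on the SF-36 physical functioning scale" and reach at least 4 on the fatigue scale), which tends to lower r. The strata may overlap with baseline function, as step 4 of the working shows.

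Three further readings are tempting and are not supported:

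- **Bias or lost power.** Omitting baseline would not bias a randomised comparison, and the stated power rests on an unadjusted test.
- **Weakened missing-data analyses.** The covariate sentence concerns treatment-effect models. The article does not list the variables in the inverse probability weights or the likelihood analysis, and it does plan to describe missing outcomes against baseline characteristics. Nothing shows that baseline severity is absent from those models.
- **The same percentages for the binary outcome.** The formula does not apply there.

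**Conclusion.** The point holds as a conditional one about efficiency. The article names ambulatory status and London ME criteria for all treatment-effect analyses and does not name the baseline score, which is collected. If that list is the operative one, the comparison is valid and the chi-squared power is unaffected. The estimates for the two primary clinical scores are then less precise than the data allow.

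The loss depends on an assumed correlation. It ranges from slight at 0.3 to substantial at 0.7, and it shrinks as the strata take up more of the baseline information. If the lodged plan already adjusts for baseline, nothing is lost and the article's sentence is merely incomplete. Either way this is an improvement available at no cost, and not a demonstrated error.

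**What to change.** Amend the covariate sentence under Analysis of quantitative data so that each treatment-effect model adjusts for the baseline value of the outcome being analysed, together with ambulatory status and London ME criteria. Check the wording against the lodged analysis plan. If the plan already specifies this, the amendment brings the article into line; if it does not, amend both together.

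The cost is one sentence. The data are already collected, and no change to sample size or assessments is needed. The article foresees a single analysis after data collection with no interim looks, so the change can still be specified in advance if it is made before outcome data are examined by arm.

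No change is asked for in the missing-data models.
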